#### Yoga program duration.

The 12-week, 36-session program is divided into two parts. The components of the yoga module are detailed in Table 2. The yoga therapist will supervise the 12-week program to ensure that participants learn asana, chanting, or meditation correctly and to prevent potential injuries. The Intervention schedule is detailed in Table 3. Although intervention will not be actively given after 12 weeks, patients will be encouraged to self-practice at home at least 3 times per week, and adherence to home practice will be monitored to assess sustained effects. For more detail, see S1 Annexure.

**Table 2 pone.0331992.t002:** Integrated Yoga Module for People Living with HIV (PLHIV).

Step	Practice	Rounds	Duration
1	Starting prayer	1	1 min
2	**Breathing Practices**	**–**	**–**
2A.	Hands stretch breathing	5	1 min
2B.	Hands in and out breathing	5	1 min
2C.	Straight leg raise breathing both legs	5	1 min
2D.	Salabhasana breathing and holding	5	1 min
3	**Loosening Exercises (Shithilikarana Vyayama)**	10 rounds each	10 min
3A.	Hand clench-Musthika Bandha	10	–
3B.	Wrist- Manibandha Naman and Chakra	10	–
3C.	Elbow -Kaponi Naman	10	–
3D.	Shoulder- Skanda Chalana	10	–
3E.	Neck-Griva Sanchalana	10	–
3F.	Knee-Janu Naman	10	–
3G.	Ankle- Goolf Naman and Chalna	10	–
3H.	Toes- Padasangula chalana	10	–
4	**Quick Relaxation Technique (QRT)**	1	5 min
5	**Asana**	1 round each	**–**
5A.	**Standing** – Ardhakati Cakrasana, Ardha Cakrasana and Padahastasana	1 round each	3 min
5B.	**Sitting-** Vakrasana **and** Janusirsasana	1 round each	2 min
5C.	**Balancing-** Vriksasana **and** Tadasana	1 round each	2 min
5D.	**Supine-** Veeparitakarani	1	1 min
6	**Pranayama**	–	–
6A.	Nadi Shuddhi	10	2 min
6B.	Ujjayi	9	2 min
6C.	Bhramari	9	2 min
7	**Deep relaxation technique (DRT)**	1	15 min
8	**Meditation**-Om Meditation	–	6 min
	**Total**	–	**60 min**

This table describes the structured sequence of the integrated yoga session, comprising breathing practices, loosening exercises, asanas, pranayama, relaxation techniques, and meditation.

Abbreviations: PLHIV = People living with HIV; QRT = Quick Relaxation Technique (QRT); DRT = Deep relaxation technique.

**Table 3 pone.0331992.t003:** Intervention schedule.

Total Contact Classes	12 contact sessions-3 sessions per week for 4 weeks
**Guided-online sessions**	24 online sessions −3 sessions per week for 8 weeks
**Total supervised yoga sessions**	36 sessions (including both contact and online sessions)
**Mode of guidance**	Subjects will be further guided through live video conferencing and pre-recorded videos
**Home practice**	During the non-contact period, participants will be encouraged to practice the yoga module for 60 minutes per day on at least 3 days per week.
**Support materials**	Picture-guided yoga booklets will be provided.

This table outlines the distribution of contact and guided-online yoga sessions delivered over a 12-week period.

### Compliance and adherence

To be compliant with the yoga intervention, every participant must attend at least 27 out of the 36 sessions (75%).

$$\text{Formula for compliance}=\frac{\text{No}.\text{ of session attended}}{\text{Total number of sessions offered }}*\text{1}\text{0}\text{0}$$

Adherence to yoga intervention is defined as a priori using both supervised session attendance and home-practice completion, details mentioned in Table 1.

### Control group

The control group will be advised to continue standard medical treatment for the same duration, along with 12 weeks of moderate-to-intensity walking (prescribed brisk walk). The duration of prescribed brisk walk will be at least practiced for a duration of 60 minutes, 3 times/week, divided into three phases: 8-minutes warm-up, 20–25 minutes of brisk walking, and followed by a 15 minutes cool-down and supine rest. Providing moderate-to-intensity walking in the control arm is intended to ensure the candidates’ interest in continuing in the control arm, reduce attrition in the control group, and not limit them from potential risk-reduction practices. Both groups will be given a logbook to track their sleep, physical activity, and medication intake. For more details, see S1 Annexure.

#### Description of the outcome measures.

The study will begin with a baseline screening visit, during which written informed consent will be obtained before starting any additional study activity. Clinical assessment, medical history, demographic characteristics, and questionnaire data will be collected at baseline and at the 3rd, 6th, and 12th-month follow-up visits. After being fully rested, all assessments will be conducted in the following order: heart rate, blood pressure, body composition, and questionnaires (Hospital Anxiety and Depression Scale (HADS), WHOQOL-HIV BREF, SF-36, Perceived Stress Scale, and the ACTG Adherence Baseline & Follow-Up Questionnaire). The primary endpoint is the change in anxiety and depression scores (HADS-A and HADS-D) from baseline to 3 months. All secondary endpoints will be assessed at baseline, 3 months, 6 months, and 12 months.

### Primary outcome measure

#### Hospital anxiety and depression scale (HADS).

In 1983, Zigmond and Snaith created the widely used Hospital Anxiety and Depression Scale (HADS), a self-assessment tool, to identify whether patients in non-psychiatric hospitals or clinics, potentially or probably have anxiety disorders or depression. The scale comprises 14 items divided into two subscales: the HADS-A (Anxiety Subscale), with 7 items assessing anxiety symptoms, and the HADS-D (Depression Subscale), with 7 items assessing depression symptoms. The scale has cut-off points for classifying symptom severity: 0–7 is normal, 8–10 is borderline abnormal (mild), and 11–21 is abnormal (moderate to severe). This tool has strong internal consistency for both measures in HIV population, with a Cronbach’s alpha of 0.83 and 0.84 for the anxiety subscale and depression subscale respectively [28].

### Secondary outcome measures

#### WHO QoL-HIV BREF.

The WHOQOL-HIV BREF is a standardized questionnaire designed to assess the quality of life (QoL) in individuals living with HIV. The internal consistency of the questionnaire ranges from 0.65 to 0.83 [29]. The questionnaire contains 31 items organized into six domains: physical health, psychological health, level of independence, social interactions, environment, and religious/personal beliefs [30].

#### SF-36 questionnaire.

It determined health status by assessing physical functioning, physical role constraints, physiological discomfort, general health perceptions, energy/vitality, social functioning, emotional role limitations, and mental health distress. The scoring ranges from 0 to 100, and the patient responds to each question with one of five options: never, rarely, sometimes very often, or always. The internal consistency reliability coefficients for the questionnaire are higher than 0.70 [31].

#### Perceived stress scale (PSS).

The Perceived Stress Scale (PSS) consists of 10 items that measure on a 5-point Likert scale (0 = Never, 4 = Very often), with higher scores indicating greater perceived stress. Some items are reverse scored to balance positive experiences. The total scores range from 0 to 40, with categories of low (0−13), moderate (14−26), and high (27−40) perceived stress. The Cronbach’s alpha for the total PSS-10 score is 0.73 [32,33].

#### Medication adherence.

A patient logbook will be given to all participants to assess self-reported physical activity, sleep, exercise duration, medication adherence through pill counts (proportion of doses taken), and attrition rate. A mean medication adherence rate below 95% will be considered suboptimal.

Self-reported adherence: How many times have you missed at least one dosage of your HIV medicine in the last 30 days?” Participants provided a number ranging from 0 to thirty. Based on this response, the “single-item self-reported adherence” for the last month will be calculated using the following method [34].

$$\text{Adherence }(\%)\;=\;\frac{\text{1}-Number\;of\;missing\;days}{\text{3}\text{0}}*\text{1}\text{0}\text{0}$$

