### The AIDS clinical trials group adherence questionnaire (ACTG-AQ)

It is a self-reported instrument that assesses HIV-positive person’s adherence to antiretroviral medication (ART). It was developed by the AIDS Clinical Trials Group (ACTG) and is intended to assess the extent to which individuals have adhered to their recommended ART regimens over the past 4 days. Questions address adherence, non-adherence, and social factors associated with adherence. (E.g. How many doses did you miss yesterday, the day before yesterday, 3 days ago, and 4 days ago?). As patients usually take more than 1 drug, so that the adherence ratio for the previous four days is calculated using formula:

$$\frac{\text{1}-(\text{number of doses missed for the day})}{\text{number of doses prescribed}},$$

by doing so, we take the numbers of different drugs and the number of pills/doses into consideration The Cronbach’s alpha for the overall standardized scores (5 items/8 variables) is > 0.80. The scale is freely accessible for academic research use [35].

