#### Statistical analysis.

The normality of continuous outcomes will be assessed using graphical methods and the Shapiro–Wilk test. Continuous variables will be summarized as mean ± standard deviation (SD) for approximately normally distributed data or median (interquartile range [IQR]) for skewed distributions, and categorical variables as frequency (percentage).

The primary endpoint at 3 months will be analyzed using an ANCOVA model, with the 3-month outcome as the dependent variable, treatment group as the fixed effect, and baseline outcome value included as a covariate. This analysis will provide adjusted between-group mean differences with 95% confidence intervals. Effect sizes will be reported to quantify the magnitude of treatment effects. Secondary outcomes assessed at 3, 6, and 12 months will be analyzed as exploratory. Longitudinal analyses will be conducted using linear mixed-effects models with fixed effects for treatment, time, and treatment × time interaction, and baseline included as an adjustment covariate. Models will be estimated using restricted maximum likelihood (REML). An unstructured covariance matrix will be specified initially; if convergence fails, an AR (1) structure will be adopted. Degrees of freedom will be calculated using the Kenward–Roger method. Robust (sandwich) variance estimators will be applied if model assumptions are violated.

Medication adherence (ACTG questionnaire and self-reported) will be analyzed as a binary outcome using logistic regression. Multivariable logistic regression models will be used to identify independent predictors of adherence, adjusting for relevant demographic and clinical covariates.

All analyses will follow the intention-to-treat (ITT) principle. Missing data will be handled using multiple imputation under a missing-at-random (MAR) assumption. The imputation model will include treatment group, time, baseline and follow-up outcomes, relevant covariates, and treatment × time interactions. A sufficient number of imputations will be generated, and convergence will be assessed using standard diagnostics. Sensitivity analyses using delta-adjusted multiple imputation / pattern-mixture models will be conducted to assess robustness to departures from MAR.

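### Both self-report adherence formulas put the '1 −' inside the numerator: the single item can never exceed 3.3%, and the ACTG ratio is right only when one dose is prescribed

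*Protocol article*

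**What the plan says.** The section 'Medication adherence' of the protocol article describes a logbook with pill counts, expressed as the share of doses taken. It then sets a threshold: "A mean medication adherence rate below 95% will be considered suboptimal". Next comes a separately labelled self-report item: "How many times have you missed at least one dosage of your HIV medicine in the last 30 days". On the answer, the text says: "Participants provided a number ranging from 0 to thirty". The score "for the last month will be calculated using the following method", and the displayed equation has a single fraction: 1 minus the number of missing days on top, 30 below, multiplied by 100.

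The next section, on the ACTG questionnaire, notes that patients usually take more than one drug and introduces a ratio for the preceding four days. The displayed fraction has 1 minus the "number of doses missed for the day" on top and the number prescribed below. The text adds that this accounts for the number of drugs and of pills or doses.

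Under 'Statistical analysis', the plan is: "Medication adherence (ACTG questionnaire and self-reported) will be analyzed as a binary outcome using logistic regression". No cut-point is given there. Neither formula appears in another form elsewhere in the article.

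**The concern.** An adherence percentage should be 100 when nothing is missed and 0 when everything is missed. Neither printed formula does this in general, because the 1 has been drawn into the numerator.

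Adherence is in the trial's title, is the fourth research question, is part of the secondary hypothesis, and is presented in the Discussion as the trial's novelty. The two scores affected are the two that the statistical section names for the logistic regression. If the printed rules are followed, one measure may carry no information on the treatment effect, and the other would partly reflect how many doses a participant is prescribed. Readers who reuse the scoring would inherit the same error.

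**Working it through.** **Inputs.** From 'Medication adherence': a 30-day window, answers m = 0 to 30, and a 95% threshold. From the ACTG section: missed doses m and prescribed doses d, with more than one drug described as usual. The count of times with a missed dose is treated as the count of missed days, as the printed formula itself does. The plan reports no worked score, so there is no figure of its own to reproduce.

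**Single item.** Printed: (1 − m)/30 × 100. Intended, by its meaning: (1 − m/30) × 100.

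| Missed days m | As printed | With the 1 outside the fraction |
|---|---|---|
| 0 | (1 − 0)/30 × 100 = 3.3% | 100% |
| 1 | (1 − 1)/30 × 100 = 0% | 96.7% |
| 2 | (1 − 2)/30 × 100 = −3.3% | 93.3% |
| 30 | (1 − 30)/30 × 100 = −96.7% | 0% |

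The printed maximum is 3.3%. Of the 31 possible answers, 29 (m = 2 to 30) give a negative percentage and none reaches 95%. Any cut above 3.3% puts all participants in one category, and a logistic regression on a constant outcome cannot estimate a treatment effect. With the 1 outside the fraction, a 95% cut separates 0–1 missed days from 2 or more.

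**ACTG ratio.** Printed: (1 − m)/d. Intended: 1 − m/d.

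| Doses prescribed d | Printed, none missed | Printed, all missed | Corrected, none / all missed |
|---|---|---|---|
| 1 | 1.00 | 0 | 1 / 0 |
| 2 | 0.50 | (1 − 2)/2 = −0.50 | 1 / 0 |
| 3 | 0.33 | (1 − 3)/3 = −0.67 | 1 / 0 |
| 4 | 0.25 | (1 − 4)/4 = −0.75 | 1 / 0 |

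The two versions agree only at d = 1. For larger d, a perfectly adherent participant scores 1/d, so the score falls as the regimen grows, although the text says that the number of doses is accounted for. The numerator is also worded per day while the ratio is described as covering four days. If the denominator were a four-day total for one dose a day (d = 4), even perfect adherence would print as 0.25.

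**Is it a conversion fault?** The other displayed fractions in the article (session compliance, waist-hip ratio, BMI) come through correctly, and the same misplacement occurs in both adherence formulas. A fault in reading the text is therefore unlikely.

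**The case against.** The best defence is that this is a typesetting slip with an obvious intended meaning. In the ACTG equation the missed doses sit in brackets that do nothing inside a numerator but make sense in 1 − (missed)/(prescribed). A statistician who saw percentages at or below 3.3% would notice. The raw answers are collected (missed times from 0 to 30, and doses missed on each of four days), so a wrong score can be recomputed without loss of data. All of this stands, and it limits the harm. It does not make the printed rule correct, and the article offers no other version to follow.

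A reader might infer that the plan's binary adherence outcome is constant and its logistic model cannot be fitted. The documents do not support that as a general statement, for three reasons:

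- The 3.3% ceiling belongs to the single item only. The ACTG ratio still varies, and for one prescribed dose it is correct.
- The 95% threshold stands next to the pill count, is worded as a mean rate, and precedes the self-report item. Applying it to the single item is the natural reading, but the statistical section does not say so.
- The pill count, as a proportion of doses taken, is not touched by either formula.

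The mix of daily and four-day wording is a weaker point. Daily ratios could be combined over four days in more than one way, and a condensed article may leave that to the full protocol.

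**Conclusion.** Both printed formulas are wrong as written. The size for the single item is 3.3%, 0% and −3.3% where 100%, 96.7% and 93.3% are meant. For the ACTG ratio it is 0.50 or 0.33 where 1.00 is meant, for perfect adherence to two or three doses.

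The loss of all variation in the single-item outcome rests on two assumptions: literal coding, and a cut above 3.3% (95% being the only one in the document). The ACTG distortion rests on literal coding and on more than one dose being prescribed, which the text calls usual.

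Severity is moderate to minor. Adherence is a secondary outcome that the plan analyses as exploratory. The HADS endpoint, its ANCOVA and the sample size are unaffected.

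**What to change.** 1. Print the single item as Adherence (%) = (1 − missed days/30) × 100.
2. Print the ACTG ratio as 1 − (doses missed/doses prescribed), with numerator and denominator covering the same period. Totals over the four days are one option; state whichever is chosen.
3. In 'Statistical analysis', state the cut used to dichotomise each measure, and say whether the 95% applies to the pill count, the single item, the ACTG ratio or all of them. This matters for the ACTG ratio: over four-day totals of 4, 8 or 12 doses, one missed dose gives 1 − 1/4 = 0.75, 1 − 1/8 = 0.875 or 1 − 1/12 = 0.917, so a 95% cut would mean no missed dose at all.
4. Check the derived scores wherever they are programmed. The article does not say that they are calculated in the Epi Info forms, so the check may belong in the analysis code.

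The cost is two corrected equations, a sentence on the cuts and a short code check. The questions put to participants do not change, and any answers already collected can be rescored.

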### The AIDS clinical trials group adherence questionnaire (ACTG-AQ)

It is a self-reported instrument that assesses HIV-positive person’s adherence to antiretroviral medication (ART). It was developed by the AIDS Clinical Trials Group (ACTG) and is intended to assess the extent to which individuals have adhered to their recommended ART regimens over the past 4 days. Questions address adherence, non-adherence, and social factors associated with adherence. (E.g. How many doses did you miss yesterday, the day before yesterday, 3 days ago, and 4 days ago?). As patients usually take more than 1 drug, so that the adherence ratio for the previous four days is calculated using formula:

$$\frac{\text{1}-(\text{number of doses missed for the day})}{\text{number of doses prescribed}},$$

by doing so, we take the numbers of different drugs and the number of pills/doses into consideration The Cronbach’s alpha for the overall standardized scores (5 items/8 variables) is > 0.80. The scale is freely accessible for academic research use [35].

### Cardiac metabolic markers

Two consecutive resting blood pressure readings will be collected at 10-minute intervals while the participants are seated, with the cuff placed on the bare upper arm, one inch above the elbow. Blood pressure will be measured with calibrated, well-functioning digital blood pressure equipment (the Omron HEM 7124 Fully Automatic Digital Blood Pressure Monitor). Waist hip measurement: To measure the waist circumference, top of the hip bone and the bottom of the ribs will be located. Participants will be asked to exhale normally, and the tape will be placed halfway between these locations, aligned with their belly button. The tape will be wrapped around the waist, keeping it slacks enough to fit one finger inside. Finally, Participant will be asked to stand with their feet together and the measurements would be recorded. The measuring tape will be wrapped around the widest point of their hips and buttocks. Measurement closest to 0.1 cm is recorded. Waist-hip ratio is measured using

$$\text{the formula}=\frac{Waist\;measurement}{Hip\;measurement}$$

$$\text{BMI is calculated using the formula}:\frac{Weight\;(Kg)}{{Height}^{\text{2}}\;(m^{\text{2}})}$$

### Sample size calculation

The sample size was determined based on a previous study, taking into account an expected mean difference of 1.54 and a pooled standard deviation of 3.38 [36]. The sample size is calculated for a two-sided independent-samples t-test to detect a standardized effect size (Cohen’s d) of 0.455, with a two-sided significance level α = 0.05, power 80%, and equal allocation (N₂/N₁ = 1). The required sample size is 154 participants (77 per group). After accounting for a 20% attrition rate, the adjusted sample size is 192 (96 participants per group).

### Recruitment procedure

Patients will be screened from the ART Clinic, AIIM, New Delhi. Eligible patients will be informed with a detailed patient information sheet explaining the study procedures, interventions, risks, and benefits of participation, confidentiality, and expectations of participants. For eligible interested participants, informed consent will be obtained in writing, and they can withdraw consent at any time.

### Randomization

Once consented, and after baseline assessment, eligible participants will be randomized (1:1 allocation ratio) using permuted block randomization. A priori, a computer-generated randomization schedule prepared by an independent statistician in randomized, permuted block lengths. Variable block sizes (4, 6, or 8) are used to ensure group balance throughout the study and minimize predictability. Multiple small block sizes are chosen to limit the risk of anticipating the next group assignment while ensuring overall group balance throughout the trial. Allocation numbers will be concealed in opaque sealed envelopes, only accessible to the study staff. The envelopes will be opened after informed consent and baseline assessment. Blinding will be maintained for the outcome assessor and statistician analyzing the data, who will be unaware of group assignments. Baseline evaluations will be done by the nursing staff, and then the randomization will be done by separate C.I.M.R. staff who will not be part of the assessment or intervention.

### Data collection and data management

EpiInfo, CDC’s free software, will be utilized for electronic data collection and management. It allows form customization, ensures standardized data entry, and provides offline data collection when the internet is unavailable. Data entry forms in Epi Info will be pre-programmed with logic checks to prevent errors during data entry. All data gathering efforts shall follow Good Clinical Practice (GCP) principles. To maintain security and consistency, data will be coded in accordance with a predefined system. Pre-defined ranges, dropdown options, and unique ID fields will be used wherever possible to minimize participant burden and improve workflow efficiency. Documents linking ID numbers with participant details will be stored separately from study data and consent forms. Each data point will be entered twice, and any differences will be flagged for resolution via source document verification. An internal research study monitor will oversee the data gathering process to guarantee accuracy, integrity, and compliance with the study protocol. The monitor will periodically evaluate data entries and validate them against the source documents. After the completion of the follow-up period for all the patients, data will be analyzed by an independent statistician, who will be blinded to the group allotment. Coded data will be handed over to the statistician while maintaining the blinding. Access to the list of participant IDs and information sheets will be restricted to the principal investigator and authorized study team members.

